### Recruitment {15}

Recruitment will take place from three main channels: (1) flyers posted around university campuses, (2) social media posts with links to the study will be posted on university-affiliated pages and through paid Facebook and YouTube adverts, and (3) through emails to list of students who access different services at the sponsor university.

Students who express interest in the study will be contacted by a member of the research team for an initial phone screen to provide more detailed information about the study and assess eligibility for the baseline assessment. The phone screen comprises of a standardised set of questions that assesses the interested student’s suicide ideation or behaviour risk, risk of harm to others and property, and mental health status (i.e. the presence of acute psychiatric symptoms in the past month) to ensure they are suitable for the baseline assessment. The phone screen will not guarantee eligibility and potential participants are informed of this at the outset. If the participant is still interested and deemed eligible at the end of the phone screen, a time is scheduled for the baseline assessment, during which eligibility is confirmed through a more comprehensive assessment.

Participants are reimbursed with a $50 e-Gift card for their time attending each of the three assessment sessions. If during the baseline assessment a student is found to be ineligible, they are reimbursed for their time with a $15 e-Gift card.

## Assignment of interventions: allocation

### Sequence generation {16a}

The baseline assessment session consists of two parts. The first confirms eligibility through an assessment of the mood and social anxiety modules in the Structured Clinical Interview for DSM-5 Research (SCID-5-RV). If a participant is found to be ineligible due to a SCID-5-RV diagnosis or the presence of risk issues, they will be referred to the Swinburne Psychology Clinic and a national crisis service (e.g. Lifeline). If a participant is eligible at the completion of the SCID-5-RV, they will be subject to random allocation using a computer-generated sequence. Randomisation to condition will be made based on Kim and Shin’s (2014) recommendation to use randomisation.com to allocate participants based on blocks to one of either Peer Tree or control.

### Concealment mechanism {16b}

There will be no concealed allocation in this trial due to the nature of the intervention. Participants will either be given Peer Tree or not and therefore explicitly know which condition they are in. The purpose of Peer Tree is to teach positive psychology strategies in an easy-to-use format and augmented with a safe, virtual space to practice and reflect on the strategies learnt. Additionally, concealment will not be viable as part of the treatment arm includes the research team establishing a close relationship with the participants in the intervention to ensure a safe environment and to help guide participants through Peer Tree to maximise the positive effects of the intervention.

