### Implementation {16c}

The sequence allocation will be generated by an independent researcher who will provide the participant’s allocation to the team member conducting the baseline assessment. This document will be stored securely on Swinburne University of Technology’s online servers and only investigators who are engaged in the project will have access to this. The document will also be password protected. The allocation will be provided to the assessor while they are in the baseline assessment via text message.

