## Assignment of interventions: blinding

### Who will be blinded {17a}

Due to the nature of the trial, no participants or researchers will be blinded to condition. Assessors will be blind to experimental condition until the end of the baseline assessment. They will request the condition from an independent researcher who will confirm the allocation to the experimental condition. Research members who conduct the assessments will also be a moderator and will help to onboard participants onto the Peer Tree platform. We opted for no blinding to allow participants to have a familiar person they can engage with on the Peer Tree platform if needed.

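### Allocation concealment is waived for reasons that concern blinding, the allocation file is open to project investigators, and the sections disagree on when each allocation is released

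*Protocol article*

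**What the plan says.** All references are to the protocol article.

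- **Concealment mechanism {16b}** waives concealment: "There will be no concealed allocation in this trial due to the nature of the intervention". It gives two reasons. The first is: "Participants will either be given Peer Tree or not and therefore explicitly know which condition they are in". The second is that "concealment will not be viable as part of the treatment arm includes the research team establishing a close relationship with the participants".
- **Implementation {16c}** describes who holds the sequence: "The sequence allocation will be generated by an independent researcher who will provide the participant’s allocation to the team member conducting the baseline assessment". The document is password-protected on university servers, and "only investigators who are engaged in the project will have access to this". On timing it says: "The allocation will be provided to the assessor while they are in the baseline assessment via text message".
- **Sequence generation {16a}** says: "The baseline assessment session consists of two parts". The first part is the SCID-5-RV eligibility interview, and an eligible participant is randomised when that interview is complete. Randomisation is in blocks; the article gives no block size.
- **Trial design {8}** also randomises once eligibility is established during the baseline assessment.
- **Who will be blinded {17a}** says: "Assessors will be blind to experimental condition until the end of the baseline assessment". It adds that assessors request the condition from an independent researcher, and that the staff who assess also moderate and help with onboarding.
- **The Abstract (Methods)** places allocation after baseline.

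**The concern.** Concealment and blinding are different safeguards. Concealment keeps the next assignment unknown to whoever decides on entry, up to the moment a person is enrolled. Blinding keeps the assignment unknown afterwards. A trial of an app against no app cannot blind its participants, but it can conceal allocation fully.

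Two things are at stake. The first is enrolment. The last entry decision is a SCID-5-RV interview, which calls for judgement, and the interviewer later works with Peer Tree participants. Someone in that position who knows the next assignment could, without intending to, let it affect who is judged eligible. Analysis cannot repair that kind of selection, and with 42 participants a few such decisions would matter.

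The second is the baseline measurement. The primary question is whether loneliness changes over time differently by group. That reading needs a baseline score taken before the arm is known.

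**Working it through.** The plan states no figure on this point, so there is nothing to reproduce. The check compares the sections and then illustrates scale.

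**1. Do the reasons in {16b} support the waiver?**
Both describe events after assignment: the participant learns the arm, and the team builds a relationship with those in the intervention arm. Neither bears on whether the next assignment can be hidden beforehand. Section {16c} shows that it can, because a researcher independent of the assessor generates the sequence and releases assignments.

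**2. Who can see the list?**
Section {16c} admits investigators working on the project. Neither {16c} nor {17a} excludes recruiters, assessors or moderators. A password does not help if the people who need to be kept out are among those admitted. The text therefore permits foreknowledge at enrolment; it does not establish it.

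**3. When is the allocation released?**

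| Section | Timing |
|---|---|
| Trial design {8} | On eligibility, during baseline |
| Sequence generation {16a} | After the SCID-5-RV, part one of two |
| Implementation {16c} | Text message during the session |
| Who will be blinded {17a} | Assessor blind to the end of baseline |
| Abstract, Methods | After baseline |

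The first three allow part two of the session to follow allocation; the last two do not.

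**4. What would a late baseline do?**
The time-by-group contrast at post-intervention is (post − baseline) in Peer Tree minus (post − baseline) in control. If knowledge of the arm moved the baseline means by δP and δC, the contrast would move by −(δP − δC), point for point. The documents give no basis for a value of δ, so none is assigned.

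**5. How predictable are allocations in 1:1 permuted blocks?**
Assumptions: the block size is 2, 4 or 6, and both it and all past allocations are known, but the list is not.

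- Block of 2: the second is always certain. Share = 1/2 = 50%.
- Block of 4: the fourth is always certain; the third is certain when the first two match (probability 1/3). Share = (1 + 1/3)/4 = 1/3 = 33%.
- Block of 6: the sixth is always certain; the fifth is certain when the last two places belong to the same arm (8/20); the fourth is certain when the first three match (2/20). Share = (1 + 0.4 + 0.1)/6 = 25%.

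A best guess is right for 75%, 71% and 68% of allocations respectively, against 50% without this knowledge. A person who can open the list is right every time.

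**The case against.** The strongest defence is that the procedure works better than {16b} describes it. The sequence comes from an independent researcher, the file is password-protected, eligibility is settled by the SCID-5-RV before randomisation, and the assessor has to ask for each allocation and gets it by text. That request would serve little purpose if assessors held the list. This stands in part: a reader might infer that enrolling staff do know the upcoming allocations, and the documents do not support that. They only fail to exclude it, while {16b} expressly disclaims concealment.

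A reader might also infer that baseline loneliness is contaminated by knowledge of the arm. That is not supported either. No section says what part two of the session contains, or that the participant is told the arm before completing the questionnaires; the text message goes to the assessor. Sections {16c} and {17a} can even be read together, with the message arriving at the end while the assessor is still in the session. That reading does not settle {8} and {16a}, which tie randomisation to the end of the eligibility interview, against the Abstract, which puts it after baseline.

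Room for judgement at entry should not be overstated. Acute symptoms are self-reported under Eligibility criteria {10} and screened with standard questions under Recruitment {15}. The SCID-5-RV is the clear instance of assessor judgement.

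Finally, a condensed article may leave block size to a fuller document, so its absence is no defect. The waiver and the access rule are not omissions: they are stated.

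**Conclusion.** The concern holds in two parts of unequal strength.

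The firmer part is enrolment. Section {16b} gives up concealment for reasons that justify only the lack of blinding, and {16c} opens the list to project staff without excluding those who enrol. Followed as written, the plan permits foreknowledge of up to 100% of upcoming allocations by anyone with access. Whether that group includes enrolling staff is not stated.

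The second part is conditional. The release timing needs reconciling whatever was done in practice. Harm to the baseline score arises only if some questionnaire is completed after the allocation is known, and the documents give no figure from which to size it.

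The 50%, 33% and 25% are illustrations under assumed block sizes, not properties of this trial. The open-label design is a separate limitation, already acknowledged, and is not the defect here.

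**What to change.** Replace {16b} with wording such as: *Allocation is concealed. The sequence is held only by the independent researcher who generated it; no recruiter, assessor, moderator or investigator can open it. Each allocation is released only once eligibility has been recorded and all baseline questionnaires have been submitted. Participants and staff are not blinded after that point.*

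Then:

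- Amend {16c} so that access to the file is limited to the independent researcher.
- Reconcile the Abstract, {8}, {16a}, {16c} and {17a} to the single release point above.
- Regenerate the unused part of the list if anyone other than the independent researcher has seen it.
- For participants already enrolled, report who had access to the list and when each allocation was released relative to completion of the baseline questionnaires.

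The cost is a change of file permission, a text message sent later in the session, and edited wording. Trial status says data collection has begun, so the access and timing changes protect only the remaining enrolments. For those already allocated, the report on access and timing is the part that still helps a reader judge the risk.

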### Implementation {16c}

The sequence allocation will be generated by an independent researcher who will provide the participant’s allocation to the team member conducting the baseline assessment. This document will be stored securely on Swinburne University of Technology’s online servers and only investigators who are engaged in the project will have access to this. The document will also be password protected. The allocation will be provided to the assessor while they are in the baseline assessment via text message.

## Assignment of interventions: blinding

### Who will be blinded {17a}

Due to the nature of the trial, no participants or researchers will be blinded to condition. Assessors will be blind to experimental condition until the end of the baseline assessment. They will request the condition from an independent researcher who will confirm the allocation to the experimental condition. Research members who conduct the assessments will also be a moderator and will help to onboard participants onto the Peer Tree platform. We opted for no blinding to allow participants to have a familiar person they can engage with on the Peer Tree platform if needed.

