## Statistical methods

### Statistical methods for primary and secondary outcomes {20a}

All data processing and analysis will occur either in the statistical package for the Social Sciences (SPSS) or Mplus. Data manipulation will only occur if the data violates the statistical assumptions for the tests that we would be conducting. In this instance, the data will be transformed into a format that does not jeopardise the interpretability of the scores.

An intention-to-treat (ITT) analysis will also be conducted on all participants who were enrolled in the project but dropped out of the study. A mixed-model analysis will be used to determine whether a greater change in loneliness occurs over time for the Peer Tree group compared with the control group. This form of analysis creates an unbiased view of the intervention by including every participant who was assigned to each group in the final analysis, rather than those who contributed to each data point in the study. That is, if 15 people were assigned to an intervention but only nine of them completed the intervention, the ITT analysis would include all 15 participants in the analysis to provide an appropriate measure of what the effect would look like with every participant included.

A per-protocol analysis using mixed-model analysis of variance will be conducted to determine whether a change in loneliness occurs over time more so for the Peer Tree group compared with the control condition. Time (i.e. baseline, post-intervention, follow-up) will be the repeated measure factor, while intervention (i.e. Peer Tree vs control) will be the between-participant factor. Two-tailed Pearson’s *r* correlations will be calculated to assess the relationships between our primary outcome, loneliness, and secondary outcomes. This will be used to determine the suitability of conducting additional, regression-based analyses. In the instances that there are violations to the assumptions of these tests, we envisage that any combination of the following will be used to answer our focal questions: standard and hierarchical regression, mediation and multiple mediation, latent trajectory modelling, *t*-tests, and mean comparisons.

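### The no-blinding rule covers all researchers, but its stated reason applies only to staff in contact with participants, so open data-handling and analysis choices may be made with arm labels visible

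*Protocol article*

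**What the plan says.** All references are to the protocol article.

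- **The rule.** Who will be blinded {17a} states: "Due to the nature of the trial, no participants or researchers will be blinded to condition". The one exception is limited in time: "Assessors will be blind to experimental condition until the end of the baseline assessment". It has ended before any post-baseline outcome exists.
- **The reason.** The same section explains: "We opted for no blinding to allow participants to have a familiar person they can engage with on the Peer Tree platform if needed". It adds: "Research members who conduct the assessments will also be a moderator and will help to onboard participants onto the Peer Tree platform". Concealment mechanism {16b} gives a related reason: "the research team establishing a close relationship with the participants in the intervention to ensure a safe environment".
- **Access to allocation.** Under Implementation {16c}, "The sequence allocation will be generated by an independent researcher". Of the allocation document it says: "only investigators who are engaged in the project will have access to this".
- **Choices left open.** Statistical methods {20a} lets the data be transformed if assumptions fail: "In this instance, the data will be transformed into a format that does not jeopardise the interpretability of the scores". It does not fix the transformation. It lists several fallback methods that may be combined, and it names a per-protocol analysis without saying who belongs to it. Criteria for discontinuing {11b} keeps withdrawn participants' data only where that is judged sensible.

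**The concern.** The rule is wider than its justification. A need for familiar staff explains why people who meet participants, or talk to them on the forum, know the arm. It does not explain why the person who scores the UCLA Loneliness Scale, checks model assumptions or picks a transformation should know it.

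This matters because loneliness is self-reported by participants who know their arm, and the assessors know it too after baseline. Masking the data-preparation and modelling stage is a safeguard that the intervention does not obstruct. Without it, a choice made in good faith can still be influenced by seeing which option favours the app. With 42 participants, small choices carry weight.

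**Working it through.** **1. Scope of the rule against scope of the reason.** The article gives no figure on this point, so the main check is a comparison of sections.

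| Role | Covered by the rule in {17a}? | Covered by the stated reasons in {17a} and {16b}? |
|---|---|---|
| Participants | Yes | Yes: they either receive the app or do not |
| Assessors, moderators, onboarding staff | Yes, after baseline | Yes: contact and familiarity |
| Anyone scoring, checking or modelling outcomes | Yes, if a researcher | No |

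**2. Does any other section mask the data?** None does.
- The numerical identifiers in the data management section protect privacy and do not hide the arm.
- The de-identified dataset described under Data safety management committee is for that committee.
- {16c} opens the allocation document to project investigators and keeps no analyst from it.

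**3. Which choices are exposed?** There are four: whether and how to transform, which fallback method to use, and who is per-protocol ({20a}), and whether withdrawn participants' data are kept ({11b}).

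**4. How large could the effect be?** The document does not supply what is needed, so this is an illustration on assumptions.
- *From the document:* 42 participants allocated 1:1 give 42/2 = 21 per arm. Twenty items scored 1 to 4 give a range of 20 to 80.
- *Assumed:* mean 45, SD 10, baseline-to-post correlation 0.6, no true effect, and a two-sample t test on change scores as a simple stand-in for the mixed model.
- *Model:* baseline = 45 + 10·Z1. Post = 45 + 10·(0.6·Z1 + 0.8·Z2), where 0.8 = √(1 − 0.6²). Scores are limited to 20–80.
- *Counted:* the share of 20,000 simulated trials with two-sided p < 0.05 in favour of Peer Tree. The nominal value is 5%/2 = 2.5%. The Monte Carlo standard error is √(0.025 × 0.975 / 20,000) = 0.11 percentage points.

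| Freedom allowed | Favourable false-positive rate |
|---|---|
| One fixed analysis | about 2.5% |
| Better of raw or log scores | about 2.9% |
| Also free to delete the Peer Tree participant with the worst change | roughly 5% to 6% |

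The range in the last row depends on whether the deletion may be tried on raw scores only or on either scale. Only the second row matches a freedom that the article leaves open, and it adds about 2.9 − 2.5 = 0.4 percentage points. The freedom over fallback methods, per-protocol membership and withdrawn data was not simulated.

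**The case against.** Four arguments deserve weight.

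- **No analyst is named.** The article does not say who processes or analyses the data, and every role described in {17a} is a contact role. A reader might infer that people who know the arms will in fact make these decisions. The text does not establish that. It states a rule with no exception for data roles, so the choices may be made unmasked. The argument stands to that extent.
- **Analyst masking is often left to an analysis plan.** That would dispose of a mere silence. Here the article answers the blinding item with a blanket statement, and a later plan with a masked analyst would have to contradict it.
- **Analysis is not the only stage where masking was possible.** A reader might infer that it is, but {17a} presents the absence of blinding as a choice made for familiarity. Nothing shows that assessor masking was impossible.
- **The larger simulated rate models something the plan does not contain.** This stands. The article does not mention outlier deletion, and {11b} concerns withdrawn participants only. The 5% to 6% figure is not an estimate for this trial.

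It is also fair to say that the direct cure for open rules is to close them. Masking protects the judgement that remains in assumption checks and model choice. The calculation above does not measure how much risk would be left once the rules are fixed.

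**Conclusion.** The point holds as an avoidable risk of bias created by a stated rule that is broader than its reason. It is not evidence that bias will occur, and its size cannot be derived from the document. For the one open choice that was simulated, raw or log scores, the inflation is small: about 2.5% to 2.9% under an assumed mean of 45, SD of 10, correlation of 0.6 and use of the freedom always in the app's favour. The higher figure may be shown only as an illustration of what selective deletion would do. This is a cheap improvement worth making, and not a flaw that invalidates the trial.

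**What to change.** Amend Who will be blinded {17a} as follows.

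1. Participants, assessors and moderators remain unblinded. Loneliness and the secondary scales are scored, checked, transformed and modelled under arm codes A and B.
2. The independent researcher in {16c} prepares this file and replaces the trial identifiers with new ones. A/B codes alone would not mask someone who can match trial identifiers to the allocation document.
3. Whoever does this pass has no access to the allocation document, the app-only variables (log-ins, acceptability, usability) or the visit dates. Dates can reveal the arm, because control participants are assessed at 6 weeks while Peer Tree participants wait for onboarding and then take 6 to 8 weeks.
4. Per-protocol membership cannot be arm-masked if it rests on app use, as the completion definition under Peer tree feasibility suggests. It is decided from usage data without sight of outcome scores.
5. The codes are released after the dataset, exclusions and model are signed off.

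**Cost.** It means preparing one recoded file, restricting access, keeping a short sign-off record and accepting a short delay. The first analysis pass should go to an existing team member who does not run assessments. No visit, sample size or treatment changes. The open rules in {20a} and {11b} still need fixing in their own right.
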